### Data analysis

The current trial aims to evaluate the safety of the combination treatment of pembrolizumab with SBRT and determine whether the sequence of these therapies matters. The primary endpoint is DLT assessed using CTCAE version 4.0. The SBRT schedule associated with DLT in <20% of patients will be determined based on the incidence of treatment-related adverse events.Response rates will be determined using RECIST v1.1. The null hypothesis that the true response rate is 0.21 [10] will be tested against a one-sided alternative. The null hypothesis will be rejected if seven or more responses are observed in 23 patients.Survival times are defined from the day of randomization until progression, last follow-up or death. Cases will be censored at last follow up visit if no progression was observed. Multivariate analysis will be performed according to the cox-regression method.For the evaluation of immunological markers, median values between two groups will be compared by the Mann–Whitney U test, between >2 groups with Kruskal–Wallis testing. To compare proportions of categorical variables, the Pearson’s Chi^2^ test or Fisher’s Exact test will be used. To evaluate correlations, Spearman correlation coefficients will be calculated. All statistical analyses will be performed using SPSS 24.0 (SPSS Inc, Chicago, IL, USA), a *P* value <0.05 will be considered statistically significant.When missing data occurs, analysis will find place with the available data. Due to the small sample size, no imputing will find place.

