#### Secondary endpoints

Objective response rate in the non-irradiated metastases as determined by RECIST v1.1 [23]. Response rate will be defined as the percentage of subjects achieving either a complete or a partial response at 12 weeks after the start of pembrolizumab. During treatment all patients will undergo a CT of the chest, abdomen and pelvis every 9 weeks or sooner if clinically indicated.Objective response rate in the non-irradiated metastases as determined by irRC [24] at 12 weeks after the start of pembrolizumab.Local control defined as the time between local irradiation and the moment the irradiated lesion shows an increase in size of ≥20%, according to the RECIST v1.1, confirmed by a consecutive assessment at least 4 weeks after first documentation.PFS defined as the time from inclusion to documented disease progression according to irRC or death from any cause.OS defined as the time from inclusion to death from any cause.

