### Follow-up

Patients will be seen before the start of each treatment cycle during the whole course of pembrolizumab therapy. At each visit, a history, directed physical examination and a routine laboratory blood analysis will be conducted with recording of the toxicity. Tumors will be re-evaluated every 9 weeks. A safety follow-up visit will find place approximately 30 days after the last dose of trial treatment or before the initiation of a new anti-cancer treatment, whichever comes first. Once a subject experiences confirmed disease progression or starts a new anti-cancer therapy, the subject moves into the survival follow-up phase and should be contacted by telephone every 12 weeks to assess for survival status until death, withdrawal of consent, or the end of the study, whichever occurs first. Subjects who discontinue trial treatment for a reason other than disease progression will move into the follow-up phase and will be assessed every 12 weeks by radiologic imaging to monitor disease status.

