### Sample size

In the first phase of the trial 20 patients will be recruited and randomly assigned to a treatment arm. If the chance that the posterior toxicity probability rate exceeds 0.2 is more than 0.7 in a certain arm, this arm will be closed.

The secondary endpoint is the assessment of the response rate of the combination treatment in non-irradiated metastases in every arm. For this analysis a Simon’s two-stage optimum design will be used [29]. The arm with the best response rate and with acceptable toxicity will be used to proceed into the second phase. The null hypothesis that the true response rate is 0.21 [10] will be tested against a one-sided alternative. If there are two or fewer responses, the alternative hypothesis will be rejected. Otherwise 13 additional patients will be accrued for a phase II trial. The null hypothesis will be rejected if 7 or more responses are observed in 23 patients. This design yields a type I error rate of 0.15 and power of 0.8 when the true response rate is 0.41 (Table 2). We consider the chance that both arms in phase 1 are deemed safe with equal toxicity and equal response rates very small. Since both arms will then qualify to continue to phase 2, selection of one arm will depend on secondary outcomes available at that time (e.g. PFS, OS).

**Table 2 Tab2:** Simon’s two-stage optimum design

Optimal two stage design	Optimum design
First stage sample size (n1)	10
r1	2
Maximum sample size (n)	23
r2	6

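### The single censoring rule for survival times depends on progression alone, which conflicts with the protocol's own PFS and OS definitions

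*Protocol article*

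**What the plan says.** Under Secondary endpoints, the protocol article defines the two survival endpoints separately. For PFS: "PFS defined as the time from inclusion to documented disease progression according to irRC or death from any cause". For OS: "OS defined as the time from inclusion to death from any cause". Both clocks start at inclusion, and progression plays no part in OS.

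Under Data analysis the two endpoints are merged. First: "Survival times are defined from the day of randomization until progression, last follow-up or death". Then: "Cases will be censored at last follow up visit if no progression was observed". The clock now starts at randomization, one list of end points serves every survival time, and censoring depends only on whether progression was seen. A multivariate Cox regression follows.

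Under Follow-up, patients with confirmed progression or a new anti-cancer therapy are "contacted by telephone every 12 weeks to assess for survival status until death, withdrawal of consent, or the end of the study". Under Sample size, PFS and OS are the examples of outcomes that would choose between the arms if toxicity and response were equal. The protocol considers that chance very small.

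**The concern.** A statistician who programs the Data analysis section as written gets endpoints that differ from those defined under Secondary endpoints. A patient who dies before progression is documented would be censored at the last visit, although the PFS definition counts that death as an event. For OS, a censoring condition based on progression has no sensible meaning.

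The protocol itself shows how such patients can arise:

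- CT is done every 9 weeks during treatment, and every 12 weeks after stopping treatment for a reason other than progression, so death can fall between scans.
- Grade 5 toxicity is among the events that count as dose limiting, so a treatment-related death before progression is foreseen.
- Patients who start another anti-cancer therapy move to telephone follow-up of survival status, so progression may never be recorded although the death is.

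Censoring these deaths is informative: it removes patients because they had the worst outcome, and PFS then looks longer than it is. If such deaths were more frequent in one arm, the comparison would favour that arm. The document gives no evidence on whether they would be.

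**Working it through.** The plan states no figure on this point, so there is none to reproduce. The check is a comparison of the two sections, followed by an illustration of size.

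**Step 1: the two sections by patient type**

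| Patient | Secondary endpoints | Data analysis, read literally | Agree? |
|---|---|---|---|
| Alive, no progression | No event for PFS or OS | Censored at last visit | Yes |
| Died, no progression observed | PFS event and OS event | Censored at last visit, although the sentence before ends the time at death | No |
| Progressed, still alive | PFS event; OS time continues | Time may end at progression; no OS censoring clause applies | PFS yes, OS no |
| Progressed, then died | PFS event at progression; OS event at death | Time may end at progression | PFS yes, OS no |

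The sections agree on both endpoints only for patients alive without progression. No other section gives a different censoring rule.

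**Step 2: possible size for PFS**

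Input: q, the share of first PFS events that are deaths without documented progression. The document gives no value, so 10%, 20% and 30% are assumed.

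Model: constant cause-specific hazards with total PFS hazard h.

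- If the deaths are censored, only the progression hazard (1 − q)h is counted.
- The median moves from ln 2 / h to ln 2 / ((1 − q)h), a factor of 1/(1 − q).
- A true PFS probability S is reported as S^(1 − q).

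Results:

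- q = 10%: 1/0.90 = 1.11; a true PFS of 40% becomes 0.40^0.90 = 0.438, about 44%.
- q = 20%: 1/0.80 = 1.25; 0.40^0.80 = 0.480, about 48%.
- q = 30%: 1/0.70 = 1.43; 0.40^0.70 = 0.527, about 53%.

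If all 20 phase I patients had a PFS event, 20(1 − q) = 18, 16 or 14 would be counted. The formula treats the patient as censored on the date of death. The rule uses the last visit, which is somewhat earlier and trims the time at risk, so the factors are approximate. With death counted as an event, this bias is zero.

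**Step 3: OS**

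The factor above does not carry over to OS, and no figure is offered. The problem there is one of definition: an endpoint that stops at progression, or is censored because progression was not seen, is not time to death.

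**Step 4: time origin**

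One section uses inclusion, the other randomization. In phase I, allocation follows enrolment, so the gap is probably small. In phase II, 13 further patients enter the one selected arm. With a single arm there is nothing to randomize, so a randomization date may not exist for 13 of the 23 patients in the response cohort.

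**The case against.** The strongest reply is that the censoring sentence should be read with the one before it. That sentence already lists death as an end of survival time, separate from last follow-up, so the next sentence may only describe patients whose time ends at last follow-up without any event. If deaths were really moved back to the last visit, the mention of death would be redundant. The endpoint definitions are also explicit and correct, and telephone follow-up of survival after progression would have no purpose if OS stopped at progression. A reader might infer that the sponsor plans to censor deaths, or to cut OS at progression. The document does not support that inference; loose drafting with PFS in mind is at least as likely.

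This stands as an account of intent, but it does not remove the conflict. The condition as written names progression only. If it was meant for PFS, it should have included death. It cannot serve OS on any reading, yet it is attached to all survival times.

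A second reply is that a condensed article leaves censoring detail to a fuller document. That would excuse silence. Here a rule is stated, and it disagrees with the endpoint definitions.

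A third reply is that little depends on it. This largely stands. The dose-limiting-toxicity endpoint, the arm-closing rule and the test of 7 or more responses in 23 patients do not use censoring. PFS and OS affect arm choice only in a tie, and even then are named only as examples.

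**Conclusion.** The point holds as an internal contradiction in a stated analysis rule. The Data analysis section conditions censoring on progression alone for every survival time. That conflicts with the Secondary endpoints definitions and with its own preceding sentence. The difference in time origin is a lesser inconsistency in the same text.

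If the rule were followed literally, median PFS would be overstated by about 11%, 25% or 43% for assumed shares of 10%, 20% or 30%. These figures rest on constant hazards and on shares that the document does not supply. They illustrate possible size and do not predict it. No size can be given for OS or for a difference between arms.

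The consequence is limited to secondary endpoints, the Cox analysis and an unlikely tie-break. It would go too far to conclude that arm selection or the trial's main conclusions are compromised. The text should still be corrected before the survival analyses are run.

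**What to change.** Replace the censoring sentence in Data analysis with two rules and align the time origin:

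- **PFS:** the event is the first of progression by irRC or death from any cause. Only patients alive without progression are censored. The last follow-up visit can remain their censoring date; nothing in this point requires changing it.
- **OS:** the event is death from any cause. Patients not known to have died are censored at the date last known alive, including dates from telephone contacts, whether or not they have progressed.
- **Time origin:** use the same origin in Secondary endpoints and Data analysis, and choose one that exists for all patients, including the 13 phase II patients in the single selected arm. Inclusion, which the endpoint definitions already use, meets that condition.

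The cost is wording only. Survival status is already followed under the existing schedule, so no new data, visits or patients are needed, and the sample size is unchanged.

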### Study approval and recruitment

This trial is approved by the Ethics committee of the Ghent University Hospital (EC2016/0661) and is registered on clinicaltrials.gov (NCT02826564).

Patient recruitment finds place at the Ghent University Hospital, Belgium. The first participant was enrolled on November 14th 2016. Participants are currently being recruited and enrolled.

Protocol version 3.0; 12th of April, 2017.

### Monitoring

Safety analysis will find place when all participants have passed 12 weeks after administration of SBRT. Immediately before allocation of a new participant, the posterior toxicity probability will be calculated by the statisticians in order to evaluate whether an arm should be terminated. Unless an arm is closed, only the statisticians will have access to the data regarding posterior toxicity probability.The trial conduct is monitored at least once annually by Bimetra Clinical Research Center Ghent and by MSD Belgium. This is independent from the investigators and the sponsor.

## Discussion

Immunotherapy has lead to breakthroughs in various solid tumors and can induce spectacular clinical responses. Yet unfortunately, responses are still only seen in the minority of patients. Several pre-clinical and clinical evidence indicate that radiotherapy instigates a systemic anti-cancer immune effect. One of these immune effects is the upregulation of PD-L1 expression and the presence of TILs in the tumor microenvironment. Therefore, the hypothesis was formed that the combination of anti-PD1 treatment with radiotherapy could work synergistically and raise response rates in patients with metastatic urothelial carcinoma. The current phase I/II trial will, firstly, investigate the safety of two different sequences of this combination treatment. In a second phase, the response rates of the combination treatment will be assessed. Throughout the study, the systemic immune effect of both treatments will be monitored on different time points. This information can aid in the fine tuning of combination therapies and may identify predictors of response or resistance to therapy or even pinpoint new potential targets for immunotherapy.

## Abbreviations

AAPM: American Association of Physicist in Medicine
aPTT: activated partial thromboplastin time
CTCAE: Common Terminology Criteria for Adverse Events
DLT: dose limiting toxicity
EDTA: ethylenediaminetetraacetic acid
ELISA: enzyme-linked immunesorbent assay
FACS: fluorescence-activated cell sorting
GTV: gross target volume
INR: international normalized ratio
irRC: immune related response criteria
OAR: organs at risk
OS: overall survival
PRV: planning organ at risk volume
PFS: progression-free survival
PT: prothrombin time
PTV: planning target volume
RECIST: response evaluation criteria in solid tumors
SBRT: stereotactic body radiotherapy
TITE-CRM: time-to-event continual reassessment method
ULN: upper limit of normal
